## SAMPLE SIZE AND STATISTICAL ANALYSIS

When comparing physical examinations by the two methods (captured by telemedicine and traditional physical examination), two statistical elements are involved, the comparison of paired proportions and the agreement between methods.

### Comparison of paired proportions

This type of comparison is usually done using the McNemmar test, as it considers the pairing of samples when comparing proportions. The sample calculation is then given considering that records from group A are paired with records from group B, this occurs in cases where two methods evaluate the same samples. McNemmar's test also considers that one wants to verify the equality of probability of a finding.

The sample size calculation requires some parameters. For our calculation, we consider four parameters. We will use the alpha of 0.05 and the statistical power (Bheta) of 0.80.

The expected total proportions of change from positive to negative and from negative to positive are also considered. For the calculation of the order of these two proportions it does not matter.

We see in the following table a combination of proportions that result in different sample sizes.

| Prop 1\Prop 2 | 0.10 | 0.15 | 0.20 | 0.25 |
|----------------------|-------------|-------------|-------------|-------------|
| 0.05          | 468  | 155         | 85          | 57          |
| 0.10          |             | 781         | 233         | 120         |
| 0.15          |             |             | 1095        | 311         |
| 0.20          |             |             |             | 1408        |

If these two proportions were too large, it would indicate that the methods are not comparable, therefore, and also for the practical aspect of the study, a sample size of 468 was chosen for the aspect of comparing paired proportions.

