## **RESEARCH LOCATION**

This study was performed in two pediatric, tertiary care and high complexity hospital (Pequeno Príncipe Hospital and Sabará Hospital), located in Curitiba and São Paulo, respectively.

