## FLOWCHART OF THIS STUDY

The single-arm, non-randomized clinical trial in second step will consist of selecting patients classified as code green (low risk), who will undergo two medical consultations and two physical examinations (Tytocare® and traditional), with the aim of comparing the results between these two modalities of examination and diagnosis. The flowchart will be as detailed in the steps below and illustrated in figure 1.

[figure not shown]

Figure 1. Flowchart of patient consultations in the study.

**Step 1:** The patient, after going through the nursing screening and being classified as code green and accepting to participate in the study, will be submitted to the first consultation with Tytocare® intervention, in the room 1. This consultation will be performed by a pediatric resident of the first year, whose inexperience should mimic that of the non-specialist doctor in the health units. The resident will collect information related to past medical history, current symptoms, and will perform a physical examination using Tytocare®. This device allows obtaining the following finding: heart rate, respiratory rate, body temperature, cardiac, pulmonary and abdominal

auscultation, otoscopy and oroscopy. In this room, Tytocare® and an attached computer will be available for data recording by the Pediatrics Resident.

**Step 2:** As the data is entered into the computer, it will be transmitted from the Tytocare® platform to the electronic system, and a second physician, called PEDIATRICIAN 1, will receive the results and images of the physical examination obtained by Tytocare®. PEDIATRICIAN 1 will be allocated in a room, called the situation room, guiding the resident and confirming the patient's care, thus configuring a second opinion on the case, thus characterizing the teleinterconsultation. These two doctors will decide together at a diagnostic hypothesis, diagnosis and/or course to be taken, which will be recorded in the data collection form (electronic document in the electronic system).

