### Concordance between methods

Verification of concordance between methods will be performed using the kappa statistical method. Again we have a combination of parameters in the calculation to establish the sample size.

Bujang's proposal (2017) uses the quantities of categories, power and alpha for the sample calculation. Assuming 80% power with an alpha of 0.05 and knowing that we have two possible categories in each response (found or not found), we have the following combination of suggested sample sizes for each combination of proportions.

| Prop 1 \ Prop 2 | 0.0 | 0.3 | 0.5 | 0.7 |
|------------------------|------------|------------|------------|------------|
| 0.2             | 194        |            |            |            |
| 0.3             | 85         |            |            |            |
| 0.4             | 47         | 698 |            |            |
| 0.5             | 29         | 169        |            |            |
| 0.6             | 20         | 72         | 563 |            |
| 0.7             | 14         | 39         | 133        |            |
| 0.8             | 10         | 23         | 54         | 363        |
| 0.9             | 7          | 14         | 27         | 79         |

Considering a statistical power of 90%, we have the following suggestion of sample sizes.

| Prop 1 \ Prop 2 | 0.0 | 0.3 | 0.5 | 0.7 |
|------------------------|------------|------------|------------|------------|
| 0.2             | 259        |            |            |            |
| 0.3             | 113        |            |            |            |
| 0.4             | 62         | 927 |            |            |
| 0.5             | 38         | 222        |            |            |
| 0.6             | 25         | 94         | 742 |            |
| 0.7             | 17         | 49         | 171        |            |
| 0.8             | 12         | 28         | 68         | 471        |
| 0.9             | 8          | 17         | 32         | 96         |

With this information, this method suggests a sample size of 698 patients (according to the proportions of the study, using the 80% power table and considering 0.3 and 0.4 proportions).

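### The 698 children are treated as independent, although residents and pediatricians at two hospitals very likely each examine many of them; this leaves kappa power without reserve and is likely to distort the McNemar p-values if examiners differ

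*Combined protocol and SAP*

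**What the plan says.** The study takes place in "two pediatric, tertiary care and high complexity hospital" (*Research location*) and plans 698 patients over an estimated ten months (*Study design*). Each child is seen twice. On the device side, "This consultation will be performed by a pediatric resident of the first year" (*Flowchart of this study*, Step 1), with PEDIATRICIAN 1 guiding remotely. On the traditional side, PEDIATRICIAN 2 examines the child (Step 3). The number of people filling each of the three roles is not given.

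*Comparison of paired proportions* chooses McNemar's test because "it considers the pairing of samples when comparing proportions", and states for it: "We will use the alpha of 0.05 and the statistical power (Bheta) of 0.80". From the table cell at discordant proportions 0.05 and 0.10, "a sample size of 468 was chosen for the aspect of comparing paired proportions". For kappa, *Concordance between methods* works from "Assuming 80% power with an alpha of 0.05" and arrives at 698, "using the 80% power table and considering 0.3 and 0.4 proportions". *Conclusion about the sample size* adopts 698.

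*Analysis of results* names paired proportions and agreement between methods. No section mentions an examiner or site effect, a design effect, an intra-examiner correlation, stratification by hospital or a robust variance. No confidence intervals are mentioned. The items listed under *Data collect* include no examiner identity.

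**The concern.** Pairing within a child is one source of dependence; sharing an examiner is another. With two hospitals, first-year residents and emergency pediatricians, and 698 children in ten months, the same people very likely see many study children each. If they differ in the threshold for calling a finding present, or in accuracy, results from children of the same examiner are correlated. Variance formulas that assume independent children then tend to be too small.

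Two things are at stake. First, McNemar's test could report a difference between device and traditional examination that is really a difference between a few examiners. That bears directly on the study's hypothesis that the two are equivalent. Second, the 80% power claimed for kappa could be optimistic.

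A separate issue concerns the estimate itself. If a finding is more common at one hospital than at the other, a single pooled kappa counts the between-hospital difference as agreement.

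**Working it through.** **1. Reproducing the plan's figures.** Inputs from the documents: alpha 0.05, power 0.80, kappa 0.3 against 0.4, discordant proportions 0.05 and 0.10. Two inputs are not stated, but they reproduce the tables: a two-sided test, and 50/50 margins for kappa.

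- Kappa: n = [(1.96·√(1−0.3²) + 0.8416·√(1−0.4²)) / 0.1]² = [(1.8697 + 0.7714) / 0.1]² = 697.5, so 698. A one-sided test would give 548.
- McNemar: n = [1.96·√0.15 + 0.8416·√(0.15 − 0.05²)]² / 0.05² = (0.7591 + 0.3232)² / 0.0025 = 468.6, against 468 stated.

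Both formulas take children as independent (design effect 1).

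**2. Power at 698 under independence.**

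- Kappa: Φ[(0.1·√698 − 1.8697) / 0.9165] = 80.0%. There is no reserve.
- McNemar: Φ[(0.05·√698 − 0.7591) / 0.3841] = 92.8%. The reserve lasts until the effective n falls to 468, a design effect of 698/468 = 1.49.

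**3. Illustrative clustering.** The number of examiners J and the intra-examiner correlation (ICC) are assumptions. Design effect DE = 1 + (m − 1)·ICC with m = 698/J; effective n = 698/DE, put into the power formulas of step 2. The same ICC range is used for both statistics only for illustration, since the correlation of agreement and that of the paired difference are different quantities.

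| J | m | ICC | DE | Effective n | Kappa power | McNemar power |
|---|---|---|---|---|---|---|
| 80 | 8.7 | 0.01 | 1.08 | 648 | 77% | 91% |
| 80 | 8.7 | 0.05 | 1.39 | 504 | 66% | 83% |
| 40 | 17.4 | 0.01 | 1.16 | 599 | 74% | 89% |
| 40 | 17.4 | 0.05 | 1.82 | 383 | 54% | 72% |
| 20 | 34.9 | 0.01 | 1.34 | 521 | 67% | 84% |
| 20 | 34.9 | 0.05 | 2.70 | 259 | 39% | 55% |

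With ICC = 0, both 698 and its 80% power stand.

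**4. How plausible the range is for kappa.** Suppose examiners differ in accuracy and prevalence is 0.5. Then P(agree) = (1 + kappa)/2, which is 0.7 at kappa 0.4, with variance 0.7·0.3 = 0.21. If resident-specific kappas have standard deviation s, the ICC of agreement is (s/2)²/0.21. For s = 0.1 this is 0.012; for s = 0.2 it is 0.048. An ICC near 0.05 therefore means kappas spread over about 0 to 0.8 (0.4 ± 2·0.2), which is extreme. About 0.01 is plausible.

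**5. Threshold differences.** A simulation used crossed examiners, 10 to 40 per role, a latent-trait model with examiner threshold SD 0.2 to 0.5 (assumed), and 3,000 runs per setting. On average the two methods did not differ.

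- McNemar: the variance of the paired difference was 1.6 to 13.6 times the independence value, and the test rejected in 12% to 59% of runs instead of 5%.
- Kappa: the variance was 0.98 to 1.40 times the independence value, and nominal 95% limits covered 90.5% to 95.6%. The main effect was a lower kappa, from 0.395 without threshold differences to about 0.31 at SD 0.5.

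**6. Pooling hospitals.** Assume equal hospital sizes, kappa 0.30 at each, and both methods at the same prevalence p within a hospital. Disagreement within a hospital is 2p(1−p)·0.7. Pooled kappa is 1 minus the mean disagreement divided by 2p̄(1−p̄).

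- p = 0.2 and 0.3: 1 − 0.259/0.375 = 0.31
- p = 0.2 and 0.4: 1 − 0.280/0.420 = 0.33
- p = 0.1 and 0.4: 1 − 0.231/0.375 = 0.38

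**The case against.** The documents state no number of residents or pediatricians, no allocation of children to them and no correlation. A reader might infer that a small pool of examiners is an established fact and that confidence limits will be too narrow. Neither follows. Repeated examiners are a strong inference from two hospitals and ten months, but still an inference. The variance is understated only if the within-examiner correlation is positive. The plan mentions no confidence intervals, so the direct effect would be on standard errors, p-values and power.

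A reader might also apply one design effect to both statistics and take 39% power as the expected outcome. The simulation argues against that: under threshold differences, kappa's variance is nearly right and McNemar's is not. The 39% needs both 20 examiners and a very wide spread in accuracy. McNemar also has a reserve that kappa lacks. The table treats clustering as a single level, while three roles are crossed, so it is a rough guide.

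The quoted sentence on pairing is itself correct. The gap is what the plan leaves out. Nor is the pooling effect necessarily large: it is 0.01 for prevalences of 0.2 and 0.3, and the documents give no prevalence by hospital.

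All of this stands and limits the size of the point. It does not remove it, because no section of the plan provides for examiner or hospital correlation.

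**Conclusion.** The concern holds in a limited form. The sample size and the planned tests treat 698 pairs as independent, in a design where examiners very likely recur. If examiners differ, the p-values are likely to be too small: strongly so for McNemar under threshold differences, and only mildly for kappa. Accuracy differences could affect kappa more.

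Kappa power has no reserve. It drops to between 77% and 66% with 80 examiners and between 67% and 39% with 20, for assumed ICCs of 0.01 to 0.05, with the low end the more plausible. McNemar's power reserve holds to a design effect of about 1.49. The simulated variance ratios all exceed that, so if they carried over to discordant proportions of 0.05 and 0.10, the reserve would cover only milder examiner variation. It does not in any case protect the p-values.

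Pooling hospitals can raise a kappa of 0.30 to between 0.31 and 0.38 under the assumed prevalences. The last value would fill most of the 0.3-to-0.4 gap on which 698 rests. The documents do not support the conclusion that 698 is too small; they support only that its 80% power depends on an unstated assumption.

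**What to change.** - Add coded IDs for the resident, PEDIATRICIAN 1, PEDIATRICIAN 2 and the hospital to the existing electronic form. State the number of clinicians per role and hospital.
- Estimate kappa and the paired difference within each hospital, then combine them.
- Base inference on a method that allows for the crossed examiner roles: a mixed model with crossed examiner effects, or a multiway cluster-robust or bootstrap variance. Clustering on one role alone would miss the others.
- State in the sample size section that the 80% power assumes no examiner clustering, and give the illustrative range above with its assumptions.

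The cost is four coded fields, a little more analysis work and somewhat wider intervals. No extra patients or staff are needed. The IDs should be in place before enrolment starts, because they may be hard to recover later.

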### Concordance between methods

Verification of concordance between methods will be performed using the kappa statistical method. Again we have a combination of parameters in the calculation to establish the sample size.

Bujang's proposal (2017) uses the quantities of categories, power and alpha for the sample calculation. Assuming 80% power with an alpha of 0.05 and knowing that we have two possible categories in each response (found or not found), we have the following combination of suggested sample sizes for each combination of proportions.

| Prop 1 \ Prop 2 | 0.0 | 0.3 | 0.5 | 0.7 |
|------------------------|------------|------------|------------|------------|
| 0.2             | 194        |            |            |            |
| 0.3             | 85         |            |            |            |
| 0.4             | 47         | 698 |            |            |
| 0.5             | 29         | 169        |            |            |
| 0.6             | 20         | 72         | 563 |            |
| 0.7             | 14         | 39         | 133        |            |
| 0.8             | 10         | 23         | 54         | 363        |
| 0.9             | 7          | 14         | 27         | 79         |

Considering a statistical power of 90%, we have the following suggestion of sample sizes.

| Prop 1 \ Prop 2 | 0.0 | 0.3 | 0.5 | 0.7 |
|------------------------|------------|------------|------------|------------|
| 0.2             | 259        |            |            |            |
| 0.3             | 113        |            |            |            |
| 0.4             | 62         | 927 |            |            |
| 0.5             | 38         | 222        |            |            |
| 0.6             | 25         | 94         | 742 |            |
| 0.7             | 17         | 49         | 171        |            |
| 0.8             | 12         | 28         | 68         | 471        |
| 0.9             | 8          | 17         | 32         | 96         |

With this information, this method suggests a sample size of 698 patients (according to the proportions of the study, using the 80% power table and considering 0.3 and 0.4 proportions).

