## PARTICIPANTS

Eligible participants in this study will be those classified as low risk (classified as green) in the triage performed by nurses in the emergency room.

Both hospitals have a risk classification protocol to stratify and classify all patients who arrive at the Emergency room. This classification is performed by the nurse and the protocol consists of five color codes (red, orange, yellow, blue and green):

- Red: serious patient, considered as an emergency, with immediate care;
- Orange: patient considered urgent, with care within a maximum period of 15 minutes;
- Yellow: patients who do not present conditions that characterize medical urgency, however, are identified as patients who require particular conditions for prioritization. As those who have comorbidities, associated with clinical conditions with potential risk for complications, with a goal of care of up to one hour;
- Green: patients who do not present clinical conditions that characterize medical urgency, with an average time of care within four hours;
- Blue: patients who have specific needs for procedures. These patients will not be classified because they do not have clinical circumstances, but they will be prioritized over those classified as non-urgent (Green), such as: tube replacement, administration of medication or dressings. Your average handle time target is two hours.

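### The kappa sample size of 698 assumes, without saying so, that each finding is present in 50% of children; for uncommon findings the power is well below the stated 80%

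*Combined protocol and SAP*

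**What the plan says.** Under Sample Size and Statistical Analysis, the plan makes two calculations: 468 for paired proportions (McNemar) and 698 for agreement (kappa). The larger is adopted in Conclusion about the sample size.

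The inputs to the kappa calculation are given as "Assuming 80% power with an alpha of 0.05 and knowing that we have two possible categories in each response (found or not found"), plus a pair of values per table cell. The choice is described as "using the 80% power table and considering 0.3 and 0.4 proportions". The plan calls these values proportions, but the tables reproduce when they are read as kappa under the null (0.3) and under the alternative (0.4). Neither this section nor any other states how often a finding is expected.

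Analysis of Results applies both analyses to the physical examination results and the diagnostic hypotheses, with no primary finding. Data Collect lists nine examination items: four vital signs, three auscultations, otoscopy and oroscopy. Enrolment means "selecting patients classified as code green (low risk"). The Participants section defines that class: "Green: patients who do not present clinical conditions that characterize medical urgency".

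**The concern.** For a found/not-found item, the variance of kappa depends on the share of patients in whom the item is found, and it rises as that share moves away from one half. A sample size that omits the share has fixed it implicitly. If the fixed value is the most favourable one, the stated power is a best case under equal margins rather than a figure for every item.

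This matters because kappa determines the size of the trial (698 rather than 468) and because the plan intends to conclude that the two examinations are equivalent. For an uncommon sign, a kappa that fails to exceed 0.3 could reflect too few positives rather than poor device performance. Kappa alone also does not show how many positive findings the two methods share, and no measure of positive agreement is planned.

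**Working it through.** **Inputs from the documents.** Two categories; alpha 0.05; power 80%; kappa k0 = 0.3 and k1 = 0.4; n = 698. Sidedness is not stated; two-sided is inferred because it reproduces the tables.

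**Input not in the documents.** Prevalence p of the finding, taken as equal for both methods.

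**Formulas.** The large-sample variance of kappa, multiplied by n, for a 2×2 table with equal margins p is

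V(k, p) = (1−k)[(1−k)(1−2k) + k(2−k) / (2p(1−p))],

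which reduces to 1−k² at p = 0.5. Then

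n = [1.96√V(k0) + z√V(k1)]² / (k1−k0)², with z = 0.842 for 80% power;

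power = Φ{[(k1−k0)√n − 1.96√V(k0)] / √V(k1)}.

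**Step 1: reproduce the plan's figure.** At p = 0.5, V(0.3) = 0.91 and V(0.4) = 0.84.

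n = [1.96 × 0.9539 + 0.842 × 0.9165]² / 0.01 = 697.5, rounded up to **698**.

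The same rule reproduces all 20 cells of the 80% table and all 20 of the 90% table. No other combination of prevalence and sidedness that was tried matches every cell of the 80% table exactly. For example, one-sided testing at 50% gives 548 for the chosen cell, and two-sided testing at 40% gives 722.

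**Step 2: change only p.** At p = 0.10, V(0.3) = 2.179 and V(0.4) = 2.205.

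Power = Φ[(0.1 × √698 − 1.96 × 1.476) / 1.485] = Φ(−0.17) = **0.43**.

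The n needed for 80% power is [1.96 × 1.476 + 0.842 × 1.485]² / 0.01, about **1,717**.

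| Assumed prevalence | Power at n = 698, kappa 0.3 vs 0.4 | n for 80% power |
|---|---|---|
| 50% | 80% | 698 |
| 40% | 79% | 722 |
| 30% | 74% | 807 |
| 20% | 64% | 1,021 |
| 10% | 43% | 1,717 |
| 5% | 27% | 3,141 |

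Simulation with 20,000 runs per point agrees: 0.79 at 50%, 0.64 at 20%, 0.43 at 10% and 0.26 at 5%.

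**Step 3: how far the loss extends.** Power stays within 2 points of 80% for prevalences of about 38% to 62%. For 0.3 against 0.5, 698 patients give 99.8% power at 20% prevalence, 95% at 10% and 76% at 5%. For 0.3 against 0.6, power is 98% at 5%.

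**Step 4: what kappa leaves unseen.** With equal margins, the share of one method's positives that the other also finds is p + k(1−p).

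- At kappa 0.4 and p = 0.10: 0.10 + 0.4 × 0.90 = 46%. Overall agreement is 1 − 2 × 0.10 × (1 − 0.46) = 89%.
- At p = 0.05: 0.05 + 0.4 × 0.95 = 43%. Overall agreement is 1 − 2 × 0.05 × (1 − 0.43) = 94%.

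So at the design's own target kappa, over half of the positives for an uncommon sign would be unmatched.

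**Step 5: what 698 can support for positive agreement.** If positive agreement is 80% (an assumption), the 95% half-width is 1.96√(0.8 × 0.2 / (698p)). Prevalences of 20%, 10% and 5% give about 140, 70 and 35 positives, and half-widths of about 7, 9 and 13 percentage points.

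**The case against.** The table arithmetic is correct, so this is an undisclosed assumption and not a miscalculation. Beyond that, three stronger readings are tempting, and the documents support none of them.

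- **That 80% power holds only at exactly 50% prevalence.** It does not: power is nearly flat from about 38% to 62%, and is still 74% at 30%.
- **That 50% is implausible in green-code children.** The documents give no prevalence. Green means non-urgent, not free of signs, and these children were brought to an emergency service. Some findings may be common. Expecting several signs to be well below 50% is reasonable, but it is an assumption.
- **That the design as a whole lacks its stated power.** The loss differs by finding and belongs to the 0.3 against 0.4 contrast, the narrowest in the kappa 0.3 column. The McNemar calculation takes discordant proportions, not prevalence, and is untouched. The four vital signs are numeric, so a found/not-found prevalence does not apply to them without a cut-off, and none is given.

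It might also be said that shared negatives dominate kappa when findings are rare. That describes raw agreement; kappa removes chance agreement. Suppose 5% prevalence, 30% of positives detected and 99% of negatives agreed. Raw agreement is 0.05 × 0.30 + 0.95 × 0.99 = 95.6%, while kappa is only 0.38.

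These limits stand, and they narrow the point. They do not remove it: an unstated input fixes the sample size, and the 80% is presented without any condition.

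**Conclusion.** The point holds conditionally. That 698 rests on 50% prevalence in both methods is established by the match to all 40 table cells. It follows that the stated 80% power for kappa 0.3 against 0.4 does not apply to uncommon findings. Which findings are affected, and by how much, cannot be settled from the documents; the range is 79% power at 40% prevalence down to 27% at 5%. These figures assume two-sided alpha 0.05, equal margins and complete data on 698 patients.

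The weakness concerns what may be claimed sign by sign. It does not show that the trial is too small for every agreement question, since wider kappa contrasts remain well powered at 10% prevalence.

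**What to change.** Keep n = 698 and make three changes.

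1. In Concordance between methods and Conclusion about the sample size, state that 80% power for kappa 0.3 against 0.4 assumes about 50% prevalence. Add the expected prevalence of each binary finding and the power at that prevalence. Where prevalence is unknown, give the range (about 64%, 43% and 27% at 20%, 10% and 5%).
2. In Analysis of Results, report positive and negative percent agreement against PEDIATRICIAN 2 for each binary sign, with 95% confidence intervals, beside kappa.
3. Make no equivalence claim for a sign whose positive-agreement interval is too wide to be informative, and fix that width before the data are analysed. The half-widths of about 7, 9 and 13 points above can guide the choice.

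Do not add AC1 or PABAK as supporting evidence, because shared negatives inflate both when findings are rare. In the 5% example, with 70% of positives missed, PABAK is 2 × 0.9555 − 1 = 0.91 and AC1 is 0.95, against a kappa of 0.38.

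The cost is wording and a few lines of analysis, with no extra patients or procedures. The downside is that the stated power becomes less favourable and some rare signs will carry no claim.
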